# A phase II open label, single arm study of hypofractionated stereotactic radiotherapy with chemoradiotherapy using intensity-modulated radiotherapy for newly diagnosed glioblastoma after surgery: the HSCK-010 trial protocol

**DOI:** 10.1186/s12885-022-09914-5

**Published:** 2022-07-29

**Keywords:** Hypofractionated stereotactic radiotherapy, Newly diagnosed glioblastoma, Adjuvant chemoradiotherapy

## Abstract

**Background:**

The most frequently diagnosed primary brain tumor is glioblastoma (GBM). Nearly all patients experience tumor recurrence and up to 90% of which is local recurrence. Thus, increasing the therapeutic ratio of radiotherapy using hypofractionated stereotactic radiotherapy (HSRT) can reduce treatment time and may increase tumor control and improve survival. To evaluate the efficacy and toxicity of the combination of HSRT and intensity-modulated radiotherapy (IMRT) with temozolomide after surgery in GBM patients and provide evidence for further randomized controlled trials.

**Methods/design:**

HSCK-010 is an open-label, single-arm phase II trial (NCT04547621) which includes newly diagnosed GBM patients who underwent gross total resection. Patients will receive the combination of 30 Gy/5fx HSRT, and 20 Gy/10fx IMRT adjuvant therapy with concurrent temozolomide and adjuvant chemotherapy. The primary endpoint is overall survival (OS). Secondary outcomes include progression-free survival (PFS) rate, objective-response rate (ORR), quality of life (Qol) before and after the treatment, cognitive function before and after the treatment, and rate of treatment-related adverse events (AE). The combination of HSRT and IMRT with temozolomide can benefit the patients after surgery with good survival, acceptable toxicity, and reduced treatment time.

**Trial registration:**

NCT04547621. Registered on 14 September 2020.

## Background

The most frequently diagnosed primary brain tumor is glioblastoma (GBM). In the United States [1], there are 2.96 newly diagnosed occurrences per 100,000 people per year while the number in China is 5 to 8. Despite definitive primary therapy including surgery, adjuvant 60 Gy/30fx chemoradiation, and temozolomide based chemotherapy [2], nearly all patients experience tumor recurrence [3] and up to 90% of which is local recurrence [4]. Thus, increasing the therapeutic ratio of radiotherapy may result in better tumor control and improve overall survival (OS).

Hypofractionated stereotactic radiotherapy (HSRT) can increase the therapeutic ratio by increasing the effectiveness and decreasing the side effects. Also, the treatment can be delivered in a shorter duration compared with conventional radiotherapy (RT). Several trials have evaluated the hypothesis of using HSRT in newly diagnosed glioblastoma multiforme (GBM) patients. Roa, et al. reported the 40 Gy/15fx HSRT improved OS compared with 60 Gy/30fx conventional RT (5.6 months vs 5.1 months, *P* < 0.05) in a randomized trial [5]. Roa et al. also reported the OS of 7.9 months using 25 Gy/5fx HSRT in elderly and/or frail GMB patients later in 2015[6]. Another randomized phase 3 trial compared temozolomide, 60 Gy/30fx standard RT and 34 Gy/10fx HSRT. For patients older than 70, the survival was better with HSRT than with standard RT (HR 0.59, 95%CI 0.37 – 0.93, *p* = 0.02). HSRT resulted in lower toxicity and shorter treatment duration.

The RTOG 93–05 reported a negative result of comparing conventional RT with carmustine alone or followed by radiosurgery [6]. To date, limited data were reported about the effectiveness of HSRT combined with intensity-modulated radiotherapy (IMRT) as adjuvant therapy in newly diagnosed GBM. With the development of HSRT techniques, there is a clear rationale for combing IMRT with HSRT to increase the treatment ratio and reduce active treatment time.

New generation automated noncoplanar HSRT delivery systems can deliver high-dose treatment and limit the dose to normal structures. However, few studies have examined the role of this new technique in newly diagnosed GBM. This study aims to evaluate the safety and effectiveness of the combination of 30 Gy/5fx HSRT and 20 Gy/10fx IMRT adjuvant therapy. The average total biological effective dose (BED) of the regimen is higher than the conventional 60 Gy/30fx treatment in our previous silico study (Fig. 1). This study can provide evidence for future non-inferiority phase III randomized controlled trials. The abbreviated course of radiotherapy can reduce the treatment time by half, benefit patients, and utilize the health resource. Thus, this study is important in potentially changing the paradigm of newly diagnosed GBM treatment.

**Fig. 1 Fig1:**
[figure not shown]
The average biological effective dose calculated using the formula BED = Total dose * (1 + (Fraction dose /α/β)), α/β ratio = 10. Silico study of 16 newly diagnosed glioblastoma patients resulted a higher BED compared with the conventional radiotherapy regimen. BED: biological effective dose; IMRT: Intensity-modulated radiation therapy; HSRT: Hypofractionated stereotactic radiotherapy

## Method/design

### Hypothesis

The hypothesis is that the combination of HSRT and IMRT with temozolomide which has the same BED compared with the conventional 60 Gy/30fx. In our previous silico study, the average BED delivered to the gross tumor volume (GTV) is higher than the conventional regimen (Fig. 1). The treatment can benefit the patients after surgery with similar efficacy and reduced treatment time. Thus, the goal is to evaluate the efficacy and toxicity of this regimen and provide evidence for further randomized controlled trials.

### Primary outcome

The primary endpoint of this open-label, single-arm phase II trial is the overall survival in GBM patients receiving hypofractionated stereotactic radiotherapy plus chemoradiotherapy after surgery.

### Secondary outcomes

To estimate the following factors:The progression-free survival (PFS) rate.The objective-response rate (ORR).The quality of life (Qol) before and after the treatment.The cognitive function before and after the treatment.The rate of treatment-related adverse events (AE).

## Study design

### Inclusion criteria

18–70 years of age;Karnofsky performance status (KPS) ≥ 60 within 14 days prior to registration;Histopathologically proved diagnosis glioblastoma multiforme;Underwent surgery, gross total resection, or subtotal resection;Estimated survival of at least 3 months;Hgb > 90/gL; absolute neutrophil count (ANC) > 1.5 × 109/L, platelets > 80 × 109/L; Creatinine < 1.5 times the upper limit of laboratory normal value; Bilirubin < 2 times the upper limit of laboratory normal value; serum glutamate pyruvate transaminase (SGPT) or serum glutamate oxaloacetate transaminase (SGOT) < 3 times the upper limit of laboratory normal value;Signed informed consent form;Agreed to participate in the follow-up.

### Exclusion criteria

Prior invasive malignancy unless disease-free;Received irradiation or other anti-tumor adjuvant therapies;Brain stem disease or tumor greater than 6 cm in maximum diameter;Isocitrate dehydrogenase (IDH) 1 or IDH2 mutations;Prior therapy with an inhibitor of vascular endothelial growth factor (VEGF) or VEGFR;Pregnancy or nursing mothers;Participated in other trials after diagnosis;Influence factors toward oral medications;Patients with Common Terminology Criteria for Adverse Events (CTCAE) 5.0 grade 3 + bleeding within 4 weeks prior to registration;Suffering from severe cardiovascular disease: myocardial ischemia or myocardial infarction above grade II, poorly controlled arrhythmias (including men with QTc interval ≥ 450 ms, women ≥ 470 ms); according to NYHA criteria, grades III to IV Insufficient function, or cardiac color Doppler ultrasound examination indicates left ventricular ejection fraction (LVEF) < 50%;Long-term unhealed wounds or fractures;History of organ transplantation;Serious diseases that endanger patients’ safety or affect patients’ completion of research, according to the researchers’ judgment.

### Withdrawal criteria

Subjects may discontinue participating in the study including but not limited to the following reasons:Progressive disease according to RANO criteria [7];Intolerable treatment-related toxicity;Protocol violation;Patient or investigator’s request;Non-compliance of the patient;Trial termination or death.

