### Sample size and power justification

The design will be a prospective single-arm phase II trial to determine the effectiveness and safety of HSRT plus chemoradiotherapy after surgery for GBM. A two-sided, one-sample log-rank test calculated from a sample of 45 subjects achieves 80% power at a 0.050 significance level to detect a hazard ratio of 0.580 when the median survival time of the historic control group is 14 months. Subjects are accrued for 12 months. Follow-up continues for 24 months after the last subject is added. Assuming a 10% loss to follow-up, the actual sample size will be 50.

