### Statistical methods

The final analysis will be done on an intent-to-treat group. The median and 95% Confidence intervals (CIs) of OS and PFS will be estimated using the Kaplan–Meier method. Overall survival will be measured from the date of treatment to the date of death or the last follow-up. Progression-free survival will be measured from the date of treatment to the date of first progression or death or the last follow-up.

ORR will be based on the proportion of patients with a best overall response of confirmed CR or PR. ORR 95% will be estimated using the exact binomial method based on the F-distribution.

EORTC QLQ-C30 (version 3.0) questionnaire will be used to evaluate the quality of life. All scales range in score from 0 to 100. The mean scores will be calculated at baseline and every 2 months after the treatment. The mean ± SD, maximum, minimum, and median values will be used to describe the measurement before and after the treatment.

Mini-Mental State Exam (MMSE, score range 0 to 30) will be used to evaluate the cognitive function. Any score of 24 or more (out of 30) indicates normal cognition. Below this, scores can indicate severe (≤ 9 points), moderate (10–18 points), or mild (19–23 points) cognitive impairment.

The mean ± SD, maximum, minimum, and median values will be used to describe the measurement before and after the treatment.

CTCAE 5.0 will be used to assess the toxicity. The number of events, number of subjects, and the incidence rate will be used to describe the measurement.

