### Evaluation, neurological, and quality of life

The assessment will be done every two months, which will include the medical history, vital signs, physical examination, KPS, blood pressure, EKG, MRI (T1 Gad enhanced, T2 FLAIR), blood routine, blood biochemistry, urine routine, stool routine, quality of life score (QLQ-C30 3.0) and cognitive evaluation (MMSE). The measure of response will be by the RANO criteria. An overview of the study assessments and procedures is presented in Table 1.

**Table 1 Tab1:** Data collection schedule

Follow-up							
	Inclusion	Surgery	RT	M2	M4	M6	Mx^a^
Consent	✓						
Medical History	✓						
Physical examinations and vital signs	✓			✓	✓	✓	✓
Blood routine, Hepatic and Renal Function	✓	✓	✓	✓	✓	✓	✓
Pregnancy Test (Childbearing Age Women)	✓						
Dosimetric MRI + CT Scan			✓				
MRI (T1 enhanced, T2 FLAIR)		✓		✓	✓	✓	✓
KPS Score	✓	✓	✓	✓	✓	✓	✓
QLQ-C30 questionnaire	✓	✓	✓	✓	✓	✓	✓
MMSE questionnaire	✓	✓	✓	✓	✓	✓	✓
Toxicity Evaluation (CTCAE 5.0)	✓	✓	✓	✓	✓	✓	✓

^a^The follow-up will be done every two months till death or the patient withdrawal from the study

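### A patient may leave the study at progression and follow-up ends at withdrawal, so overall survival, the primary endpoint, can be informatively censored and biased upward

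*Protocol article*

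**What the plan says.** All references are to the protocol article.

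- **Primary outcome:** "The primary endpoint of this open-label, single-arm phase II trial is the overall survival in GBM patients" who receive the regimen.
- **Withdrawal criteria:** "Subjects may discontinue participating in the study including but not limited to the following reasons:Progressive disease according to RANO criteria [7"]. The same list contains intolerable toxicity, protocol violation, a request by patient or investigator, non-compliance, and trial termination or death.
- **Table 1, footnote a** (Evaluation, neurological, and quality of life): "The follow-up will be done every two months till death or the patient withdrawal from the study".
- **Statistical methods:** "Overall survival will be measured from the date of treatment to the date of death or the last follow-up". Also "The median and 95% Confidence intervals (CIs) of OS and PFS will be estimated using the Kaplan–Meier method", and "The final analysis will be done on an intent-to-treat group".
- **Sample size and power justification:** a two-sided one-sample log-rank test with 45 subjects, 80% power, alpha 0.05, hazard ratio 0.580 against a historical median of 14 months, 12 months of accrual and 24 months of further follow-up. Then: "Assuming a 10% loss to follow-up, the actual sample size will be 50".
- **Abstract, Background:** "Nearly all patients experience tumor recurrence and up to 90% of which is local recurrence".

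**The concern.** Read together, these passages give a route by which OS is cut off at progression. Progression is a listed reason to leave the study, leaving ends follow-up, and a patient without a recorded death is censored at the last follow-up.

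Kaplan–Meier estimation and the one-sample log-rank test both require that a censored patient has the same future risk of death as a comparable patient still under observation. A glioblastoma patient who has just progressed does not meet that requirement. Removing such patients takes out deaths faster than it takes out expected deaths, so the bias runs towards benefit. There is no concurrent arm to share the bias, because the reference is a fixed historical median.

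The group exposed to this is large, since the protocol itself expects nearly all patients to recur. Raising 45 to 50 for loss replaces lost information, but it does not correct loss that is related to prognosis. Because withdrawal is discretionary in an open-label trial, whether a death is counted could also depend on a local decision.

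**Working it through.** **1. The plan's own figure.** Exponential survival, uniform accrual over 12 months, 24 months of further follow-up.

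- Control hazard λ0 = ln 2 / 14 = 0.0495 per month. Alternative λ1 = 0.58 × λ0 = 0.0287, median 14 / 0.58 = 24.1 months.
- Probability of an observed death: p(λ) = 1 − [exp(−24λ) − exp(−36λ)] / (12λ). This gives p(λ0) = 0.770 and p(λ1) = 0.575. With n = 45, expected deaths are 34.7 under no benefit and 25.9 under the alternative.
- One-sample log-rank sample size with null variance: N = (√v0 × 1.960 + σ × 0.842)² / (v1 − v0)². Here v1 = 0.575, v0 = v1 / 0.58 = 0.992, and σ² = 0.936 is the per-patient variance of observed minus expected deaths under the alternative. N = (1.952 + 0.814)² / 0.4166² = 44.1, and power at n = 45 is 0.81.
- Loss: 45 / 0.90 = 50.

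The stated 45 and 50 reproduce. They assume that deaths are observed throughout the 24 to 36 months available per patient.

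**2. What withdrawal at progression does.** The protocol gives neither the timing of progression nor the share of progressing patients who would leave, so both are assumptions. In both models the true median OS is 14 months (no benefit), n = 45, Z = (O − E)/√E with E from λ0, and a false claim of benefit is Z < −1.96.

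- *Model A:* exponential time to first event (progression or death) with median 6, 8 or 10 months. Of first events, 10, 20 or 30% are deaths. Survival after progression is calibrated so that median OS is 14 months. This makes nine scenarios.
- *Model B:* exponential OS. 95% of patients progress before death, on average halfway to death.

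| Share of progressing patients who leave | Model A, false benefit (range of 9) | Model B, false benefit | Model B, typical KM median (months) | Model B, mean deaths |
|---|---|---|---|---|
| 0% | below 0.5% | 1.9% | 13.9 | 34.6 |
| 10% | 0.1–1.3% | 4.2% | 15.0 | 31.3 |
| 25% | 0.8–7% | 12% | 16.8 | 26.4 |
| 50% | 3–48% | 44% | 21.3 | 18.3 |
| 75% | not run | 90% | 30.8 | 10.1 |
| 100% | 23% to about 100% | about 100% | not reached | 1.7 |

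If all progressing patients leave, Model A deaths fall from about 37–38 to about 4–13, and O/E falls to 0.14–0.70. Repeat runs put the low end of its false-benefit range at 22 to 23%.

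**3. A caution on the Model A baseline.** Only its median is matched to 14 months, so OS is not exponential and O/E is about 1.07–1.13 even with full follow-up. Its error rate with no one leaving is therefore below the nominal 2.5% for a reason unrelated to censoring. Model B satisfies the test's null, and its 1.9% is the fairer baseline.

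**4. With complete survival follow-up** Model B gives power 0.82 under hazard ratio 0.58 with about 26 deaths, so the design performs as stated.

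**The case against.** A reader might infer that OS *is* censored at progression for every patient. The text does not support that. Withdrawal criteria says that subjects *may* discontinue, and keeping a progressing patient under follow-up also complies. The analysis section defines PFS and OS as separate endpoints and contains no rule that censors OS at progression. The 24 months of further follow-up, the 10% loss allowance, the intent-to-treat statement and the inclusion criterion on agreeing to follow-up all suggest that the authors meant to observe deaths. The footnote could also be read as the patient's own withdrawal only. A condensed article may leave vital-status procedures to a fuller document.

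Much of this stands. It makes the bias conditional, and it means the all-leave figures are a worst case. If 10% of progressing patients leave, Model A stays below the nominal 2.5%.

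It does not remove the point. The article does more than stay silent: it says when follow-up stops, under a heading that uses the same word, withdrawal, for progression. Intent-to-treat keeps a withdrawn patient in the analysis but supplies no date of death. The follow-up that patients agree to is the one that ends at withdrawal. An analysis plan cannot recover deaths that were never collected.

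A reader might also infer that late neurotoxicity goes unobserved. That is too strong. The late window opens 3 months after radiotherapy, and with an assumed median of 6–10 months to progression or death most patients would reach it. For those who leave, late-toxicity, quality-of-life and MMSE follow-up can be cut short.

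**Conclusion.** The concern holds in conditional form. As written, the protocol allows OS to be censored at progression for any patient withdrawn then, and the resulting bias is towards benefit. The size depends on a share that the document does not give. Over both models the probability of a false claim of benefit is about 0.1–4% at 10% leaving, 1–12% at 25%, 3–48% at 50%, and 23% to about 100% if all leave. Those figures rest on the assumed timing of progression, the assumed proportion of patients who progress before death, and no contact after withdrawal. Because the endpoint at risk is the primary one and missing deaths may be impossible to recover later, the wording should be settled before the data are relied on.

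**What to change.** Reconcile Withdrawal criteria, the Table 1 footnote and the OS definition in Statistical methods:

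1. State that leaving the study for progression, toxicity, protocol violation or non-compliance does not end survival follow-up. Vital status is collected, by telephone if needed, until death or the data cut-off, unless the patient withdraws consent to follow-up.
2. Change the Table 1 footnote so that follow-up runs to death, withdrawal of consent to follow-up, or data cut-off.
3. State that OS is not censored at progression or at the start of new therapy.

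This proposes no rule on when treatment should stop. The cost is a short wording amendment and the additional survival-status contacts. The sample size stays at 45 (50 with loss).

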## Methodology

### Treatments

The regimen will be 3 major parts.IMRT radiotherapy;HSRT radiotherapy;Temozolomide systemic treatment.

IMRT is recommended to be administered within 3 to 5 weeks after the surgery. A magnetic resonance imaging (MRI) and computerized tomography (CT) scanning obtained with the patient immobilized in the treatment is required for treatment planning. The gross tumor volume (GTV) will be defined by T1 enhancement and either the FLAIR or T2 abnormality on the postoperative MRI scan. The clinical target volume (CTV) will be defined by the GTV plus a margin of 2 cm to include the tumor subregion. The planning tumor volume (PTV) will be defined by the CTV plus a margin of 3 to 5 mm to account for the set-up and localization. It can be acceptable to reduce the PTV margin if the organ at risk (OAR) is not permissible. The PTV will be treated to 20 Gy in 10 fractions, once daily. The IMRT treatment will be finished within 2 weeks. The acceptable plan will be defined as >  = 90% of PTV covered by 20 Gy and >  = 97% of PTV covered by 18 Gy. The unacceptable plan will be defined as < 90% of PTV covered by 20 Gy and < 97% of PTV covered by 18 Gy.

The HSRT treatment should be administered within 3 days after the IMRT. The GTV will be defined by the contrast-enhanced MRI T1 scan and the surgical cavity margins. The CTV will be defined by the GTV plus a margin of 5 mm, and the PTV will be the same as the CTV. The HSRT treatment should be administered within 3 days after the IMRT. The PTV will be treated to 30 Gy in 5 fractions once daily, and an iso-dose line of 60–70% will be acceptable. The radiotherapy combination will be 30 Gy/5fx HSRT and 20 Gy/10fx IMRT. The total biological effective dose (BED) of the PTV is 72 Gy in a ratio of alpha/beta ratio of 10, which equals the conventional 60 Gy/30fx treatment but halved the duration.

Temozolomide will be administered on the first day of IMRT concurrently till the last day of HSRT at a daily oral dose of 75 mg/m^2^. Temozolomide is recommended to be taken in the morning. Post-radiation temozolomide will be administered 28 days after the last day of radiotherapy. A variation of 3 days will be acceptable. The first cycle will be 150 mg/m^2^ daily for 5 days of a 28-day cycle. If no > grade 2 toxicity is observed. The following treatment will be temozolomide 200 mg/m^2^ for at least 6 cycles (Fig. 2).

**Fig. 2 Fig2:**
[figure not shown]
The workflow of the study. GBM: Glioblastoma multiforme; IMRT: Intensity-modulated radiation therapy; HSRT: Hypofractionated stereotactic radiotherapy; MRI: magnetic resonance imaging; MRS: magnetic resonance spectroscopy; PET: positron emission tomography

### Sample size and power justification

The design will be a prospective single-arm phase II trial to determine the effectiveness and safety of HSRT plus chemoradiotherapy after surgery for GBM. A two-sided, one-sample log-rank test calculated from a sample of 45 subjects achieves 80% power at a 0.050 significance level to detect a hazard ratio of 0.580 when the median survival time of the historic control group is 14 months. Subjects are accrued for 12 months. Follow-up continues for 24 months after the last subject is added. Assuming a 10% loss to follow-up, the actual sample size will be 50.

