### Project duration and expected outcomes

The estimated period of inclusion time will be 1 year. The estimated study completion date will be the end of 2021. And the follow-up duration will be 2 years. The complete duration is estimated to be 3 years.

The study is expected to have a similar PFS, and OS compared with the survival of standard chemoradiation reported by Stupp. If the result supports the hypothesis, a non-inferiority phase III randomized controlled trial will be conducted to provide higher evidence to support this regimen. The abbreviated course of radiotherapy can reduce the treatment time by half, benefit patients, and utilize the health resource.

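### The trial is sized to show superiority (hazard ratio 0.58, about 24 versus 14 months), but its hypothesis and its condition for phase III are similar survival, which this test cannot support

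*Protocol article*

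**What the plan says.** Three sections of the protocol article bear on the point.

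- **Sample size and power justification.** "A two-sided, one-sample log-rank test calculated from a sample of 45 subjects" is said to give 80% power at the 0.05 level "to detect a hazard ratio of 0.580 when the median survival time of the historic control group is 14 months". Accrual lasts 12 months, follow-up 24 months after the last entry, and 45 becomes 50 for 10% loss.
- **Hypothesis.** "The treatment can benefit the patients after surgery with similar efficacy and reduced treatment time". The reasoning is that the regimen delivers the same biologically effective dose as the conventional course in half the time.
- **Project duration and expected outcomes.** "The study is expected to have a similar PFS, and OS compared with the survival of standard chemoradiation", followed by "If the result supports the hypothesis, a non-inferiority phase III randomized controlled trial will be conducted".

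The Statistical methods section adds a Kaplan–Meier median with a 95% confidence interval for OS.

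**The concern.** The only powered test asks whether survival is better than a 14-month control. The hypothesis says it will be about the same. A significant favourable result would therefore show something the hypothesis does not claim, and is very unlikely if the hypothesis is true. A non-significant result is what the hypothesis predicts, but it cannot separate similar survival from moderately worse survival.

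At stake is what the trial may conclude on its primary endpoint, and whether the one stated condition for moving to phase III can be met by any result of the planned test. With no concurrent control arm, there is no internal comparison to settle the matter.

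**Working it through.** **Inputs, all from the sample size section:** one-sample log-rank test, two-sided 0.05; power 80%; hazard ratio (HR) 0.58; control median 14 months; accrual 12 months; further follow-up 24 months; 45 evaluable, 50 enrolled. **Assumptions:** exponential survival and uniform accrual.

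**1. Implied target.** Control hazard = ln 2/14 = 0.0495 per month. Target median = 14/0.58 = 24.1 months.

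**2. The plan's own figure.** Under HR 0.58 the event probability is p1 = 0.575, the expected null cumulative hazard per patient is v0 = 0.575/0.58 = 0.992, and the variance of O−E per patient is s2 = 0.936.

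n = (1.96·√0.992 + 0.842·√0.936)² / (0.575 − 0.992)² = 44.1, rounded up to 45.

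Power at 45 is 80.8% by formula and about 83% by simulation, and 45/0.9 = 50. The stated size reproduces; its arithmetic is not the problem.

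**3. What the test returns if the hypothesis is true or survival is worse.** Simulated trials with n = 45 and Z = (O−E)/√E, where O is observed deaths and E is deaths expected at the control hazard:

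| True HR | Median (months) | Significant benefit | Non-significant |
|---|---|---|---|
| 0.58 | 24.1 | 83% | 17% |
| 1.0 | 14.0 | 2% | 95% |
| 1.2 | 11.7 | <1% | 78% |
| 1.25 | 11.2 | <1% | 70% |
| 1.3 | 10.8 | <1% | 61% |

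Using the average of O and E as the variance moves the 2% to about 3%.

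**4. Where the test becomes significant.** The observed O/E must be about 0.70 to 0.72 or lower, a median of about 14/0.70 = 20.0 to 14/0.72 = 19.4 months.

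**5. What a result exactly on the control rate would show.** At HR 1 about 35 deaths are expected (45 × 0.770 = 34.7). With O = E = 35 the exact Poisson 95% interval for the HR is 0.70 to 1.39, or medians from 14/1.39 = 10.1 to 14/0.70 = 20.0 months. That is compatible with both clear benefit and clear harm.

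**6. What the same size gives if similarity is the goal.** Suppose the criterion is that a lower confidence bound excludes a named unacceptable median, and the true median is 14 months. The reference medians below are illustrative; the article names none. Power for 45 evaluable patients, to within about a percentage point:

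| Median to exclude (HR versus 14) | One-sided 0.05 | One-sided 0.025 |
|---|---|---|
| 9.5 months (1.47) | 75% | 63% |
| 10 months (1.40) | 63% | 51% |
| 11 months (1.27) | 40% | 28% |

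One-sided 0.025 corresponds to the plan's two-sided 0.05. Counting all 50 as fully followed would raise the one-sided 0.05 column to about 79%, 68% and 44%, but this ignores the 10% loss that the plan itself allows for.

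**The case against.** Four arguments on the other side deserve weight.

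- **No rule equates non-significance with support.** This stands. A reader might infer that a clearly worse regimen would usually be carried forward as similar. The article does not support that: the phase III sentence attaches no statistic to support for the hypothesis, and the Kaplan–Meier median and its interval will be reported. If support meant an estimate no worse than control, a regimen with true HR 1.25 would reach O/E of 1.0 or less in only about 8% of trials. With an illustrative cut-off of 1.1 it would be about 21%. The 61% to 78% figures are rates of non-significance only.
- **The article also speaks of improvement.** This stands in part. The Abstract and Background say the approach may improve survival, and the in-silico study reports a higher average biologically effective dose than the conventional course. So it would be too strong to say that the powered effect has no basis in the text. But these are motivation; the section headed Hypothesis and the phase III condition both speak of similarity.
- **This is a condensed article, and a decision threshold may sit elsewhere.** Agreed: the lack of a numerical go rule or margin is not the point. The point is two published statements that do not agree. A similarity margin held in another document would still not match the test that sizes the trial.
- **A single-arm phase II cannot establish non-inferiority, and the article defers that to phase III.** Also true, and the deferral is reasonable. It does not explain how a test for HR 0.58 would inform the step.

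**Conclusion.** The point holds as a mismatch between the powered test and the stated hypothesis. The sample size calculation is correct for a median of about 24 versus 14 months. If survival is truly similar, the test shows a benefit about 2% of the time and is non-significant about 95% of the time. That result is not evidence of similarity, because it is also the more frequent one at true hazard ratios of 1.2 to 1.3. The planned analysis as powered therefore cannot deliver the support on which phase III is made conditional.

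The figures rest on exponential survival, uniform accrual, 45 fully followed patients and a fixed 14-month control. Another variance for the test shifts them by a few percentage points and leaves the conclusion unchanged. They say nothing about how often phase III would actually be launched.

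**What to change.** Make the Hypothesis, Sample size and Expected outcomes sections agree. No patients need be added. Either:

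- **A. Keep the superiority test.** State the target as improvement over 14 months (about 24 months under exponential survival), remove similar OS as the expected result, tie the phase III sentence to that target, and state that a non-significant test is not evidence of similarity.
- **B. Keep similarity.** Make the primary criterion a confidence bound for OS that must exclude a pre-named unacceptable median. State the one-sided level and give the power for 45 evaluable patients, as in the last table under the working. The sponsor must choose and justify the unacceptable median; 9.5, 10 and 11 months are only illustrations.

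The cost is rewording and, under B, a less favourable stated power: 50 enrolled patients can exclude only a large deficit with reasonable probability. A tighter claim would need a larger trial. For example, with an assumed margin of HR 1.25 against the fixed control, one-sided 0.025 and 80% power, events = (1.96 + 0.842)²/(ln 1.25)² = 158, or 158/0.770 = about 205 patients before loss. Under A, the cost is that the trial no longer claims to test the shorter course as equivalent in survival.
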